## **8.11. Pharmacokinetic Assessments**

### **8.11.1. Pharmacokinetic Blood Sample Collection**

Blood samples for PK analysis will be taken based on Treatment. For subjects who terminate early from the study, a blood sample for PK analysis should be collected; the PK time point closest to the ET time and the relative dosing day shall be recorded in the appropriate eCRF.

A total of 116 blood samples (approximately 3 mL each) will be collected from each subject for PK determination. The estimated total blood volume per subject for PK analysis is expected to be 394 mL. See [Appendix 1](#) for the estimated total volume of blood collected from each subject over the course of the study.

#### **8.11.1.1. Treatment A (Nimodipine Infusion) Pharmacokinetic Blood Sample Collection**

*Note: PK and clinical venous blood sampling should occur in the arm opposite to infusion, and the infusion line should not be used for PK sampling.*

- Day 1: Pre-dose (time 0, before initiation of the first [8 AM] infusion), and at 0.33, 0.5, 0.75, 1, 1.33, 2, 3, and 4 hours post initial (8 AM) dose.
- Starting on Day 3, blood samples for PK should be taken at: 48 (prior to initiation of the 8 AM 4 mg dose), 48.33, 48.5, 48.75, 49, 49.33, 50, 51, 52, 52.33, 52.5, 52.75, 53, 53.33, 54, 55, 56, 56.33, 56.5, 56.75, 57, 57.33, 58, 59, 60, 60.33, 60.5, 60.75, 61, 61.33, 62, 63, 64, 64.33, 64.5, 64.75, 65, 65.33, 66, 67, 68, 68.33, 68.5, 68.75, 69, 69.33, 70, 71, 72-hours post-start of first infusion.
- Note, for timepoints that are scheduled at the same time as the 4 mg dose (48, 52, 56, 60, 64, 68, and 72 hours post-start of infusion), blood for PK analysis should be taken before initiation of the 30-minute infusion. For the 0.5, 48.5, 52.5, 56.5, 60.5, 64.5, and 68.5-hour timepoints, blood samples for PK analysis should be collected after completion of the 4 mg infusion.

#### **8.11.1.2. Treatment B (Oral Nimodipine) Pharmacokinetic Blood Sample Collection**

*Note: Subjects will take a total of 18 oral doses during the 72 hours of treatment, administered q4h starting at approximately 8 AM on Day 1 (e.g., 8 AM, 12 PM, 4 PM, 8 PM, 12 AM, 4 AM).*

- Day 1: Pre-dose (time 0, before the first [8:00 AM] dose), and at 0.33, 0.5, 0.75, 1, 1.33, 2, 3, and 4 hours post initial (8:00 AM) dose.
- Day 3, blood samples for PK should be taken at: 48 (prior to initiation of the 8:00 AM 60 mg dose), 48.33, 48.5, 48.75, 49, 49.33, 50, 51, 52, 52.33, 52.5, 52.75, 53, 53.33, 54, 55, 56, 56.33, 56.5, 56.75, 57, 57.33, 58, 59, 60, 60.33, 60.5, 60.75, 61, 61.33, 62, 63, 64, 64.33, 64.5, 64.75, 65, 65.33, 66, 67, 68, 68.33, 68.5, 68.75, 69, 69.33, 70, 71, 72-hours since the first dose.
- Note, for timepoints that are scheduled at the same time as the 60 mg oral dose (48, 52, 56, 60, 64, 68, and 72 hours since first dose), blood for PK analysis should be taken before oral dose intake.

### **8.11.2. Pharmacokinetic Assessment Windows**

Deviations from the scheduled sample collection time of  $\pm 5$  minutes for samples at 0.25 through 3 hours post-dose and  $\pm 10$  minutes for all samples at  $>3$  hours post-dose will not be considered protocol deviations.

Pre-dose (time 0) blood samples must be collected before dosing. The exact time of study drug administration (oral dose time, and both start and stop times for both the 30-minute IV infusions and the continuous IV infusion) and the blood sampling for PK assessments will be recorded in the eCRF.

### **8.11.3. Bioanalytical Analysis**

From each blood sample, plasma will be harvested and stored frozen (at approximately  $-70^{\circ}\text{C}$ , or approximately  $-20^{\circ}\text{C}$  if  $-70^{\circ}\text{C}$  is not available), at the bioanalytical laboratory. Details of PK blood sample collection, processing, storage, and shipping will be provided in a separate laboratory manual.

Analysis of plasma concentrations of nimodipine will be performed using a validated method of liquid chromatography with tandem mass spectrometry (LC-MS/MS).

### **8.12. Safety**

The safety assessments will include the nature, frequency, and severity of AEs by treatment group, laboratory safety parameters (hematology, biochemistry, coagulation, and urinalysis), SBP, DBP, other vital signs (pulse rate, respiration, and temperature), physical exam findings, and 12-lead ECGs.

Details of AE assessments are provided in Section 9.

### **8.13. Concomitant Medication**

At Screening and at the time points indicated in the Time and Events Scheduled (Table 4-1), a qualified member of the research staff will query subjects about medication (prescription or non-prescription), herbal remedies, nutritional supplements, or topically applied treatments the subject is using or has used. Concomitant medications will be coded using the World Health Organization drug dictionary (WHO-DDE, Version March 2017, Anatomical Therapeutic Chemical classes [ATC Level 4]). This information will be documented in the source documents and eCRFs and used to determine whether the subject qualifies to continue in the study.

### **8.14. Assessment Windows**

All assessments designated as pre-dose should be completed prior to the dose time as recorded in the eCRF.

PK assessment windows are provided in Section 8.11.2.

Vital sign measurements:  $\pm 15$  minutes from scheduled time point. At any point that requires measurement of vital signs at the same time as blood collection, vital signs (especially BP) and/or the ECG should be collected BEFORE blood is drawn.

## **8.15. Other Study Procedures**

### **8.15.1. Nausea or Vomiting**

If nausea or vomiting occur, treatment with promethazine is permitted. If resolved, the subject can remain in the study.

### **8.15.2. Potential Pregnancies**

If it is determined that a subject is pregnant based on the laboratory results at Screening or at admission to the CRU, the site should screen fail the subject and refer her to her physician (providing her a copy of any relevant laboratory reports). If a subject is found to be pregnant any time after admission to the CRU until 30 days after the last dose of study medication, it should be reported to the Investigator and followed through the completion of pregnancy and 6 to 12-month follow-up of the newborn, or as appropriate.

### **8.15.3. Unplanned infusion interruptions:**

See [Table 8-2](#) for summary of algorithm. If interruptions occur to drug administration due to IV-specific issues (i.e., pump failure, infiltration, unintentional IV removal) the infusion will be restarted as quickly as practical. If the interruption(s) occurs during the initial 30 minute, high-rate infusion period, and the interruption(s) total to <3 minutes, then the high-rate infusion time and 0.5 hour blood sample collection time will extend accordingly (e.g., if the high-rate IV infusion is interrupted at 15 minutes, and is restarted in three minutes, the infusion is stopped from 15 minutes to 18 minutes, so the high-rate infusion period will continue for an additional 3 minutes, to 33 minutes), at which point (33 minutes) the nominal 0.5 hour sample will be collected. The timing of these events will be noted in the eCRF. If the experienced interruptions to the high-rate infusion on Day 1 is greater than or equal ( $\geq$ ) to 3 minutes for any given q4h dosing cycle on Day 1, the subject will be released from the CRU for that day. The subject may return to the CRU the following day, at which point the Day 1 will be repeated. This deviation will be recorded by the principal investigator.

If infusion interruption occurs during the high-rate infusion on Days 2, the infusion will be restarted as quickly as possible. Infusion interruptions during high-rate infusion on Day 2 will not result in withdrawal of the subject.

On Day 3, similar criteria as for Day 1, will apply if the interruption(s) total to <3 minutes during the high-rate infusion period for any given q4h dosing cycle, i.e., the timing of the end of infusion sample will be adjusted so that it occurs at the end of infusion at this rate (e.g., if the infusion is interrupted for 3 minutes, the end of infusion sample will be collected at 33 minutes after the start of the high-rate infusion, rather than 30 minutes). The nominal time for other samples (e.g., 48.75, 49, 50 hours) will be unchanged. If the total interruption during during any given q4h dosing cycle exceeds 3 minutes on Day 3, the patient will be withdrawn from the study and replaced. Infusion interruptions during high-rate infusion on Day 2 will not result in withdrawal of the subject.

On Day 3 if interruptions occur to the drug administration due to IV-specific issues during the low-rate infusion period the infusion will again be restarted as quickly as possible. If the total duration of interruptions of the low-rate infusion during Day 3 exceeds 30 minutes, during any given q4h dosing cycle that patient will be withdrawn from the study and will be replaced. Interruptions of infusion during low-rate infusion on Days 1 and 2 will not result in withdrawal

of the subject. Interruptions of infusion during the low-rate infusion will not alter sample collection times. See Table 8-2 for summary of algorithm.

**Table 8-2. Action to be Taken for Infusion Interruptions**

|                                    | Day 1                                                                                                                                                                                                                                                                                                                                                                   | Day 2                                                                                | Day 3                                                                                                                                                                                                                                                                                                                                                                       |
|------------------------------------|--------------------------------------------------------------------------------------------------------------------------------------------------------------------------------------------------------------------------------------------------------------------------------------------------------------------------------------------------------------------------------|---------------------------------------------------------------------------------------------|------------------------------------------------------------------------------------------------------------------------------------------------------------------------------------------------------------------------------------------------------------------------------------------------------------------------------------------------------------------------------------|
| Interruption in high-rate infusion | Restart infusion as quickly as practical. If total interruption $\geq 3$ minutes in any q4h dosing cycle, discharge subject, restart the following day. If total interruption $< 3$ minutes total interruption, adjust nominal 0.5-hour sample to occur at the end of infusion. Other nominal time points will be unchanged. Document timing of infusion interruption in eCRF. | Restart infusion as quickly as practical. Document timing of infusion interruption in eCRF. | Restart infusion as quickly as practical. If total interruption $\geq 3$ minutes in any q4h dosing cycle, subject to be withdrawn and replaced. If total interruption $< 3$ minutes for any given q4h dosing cycle, adjust nominal 0.5-hour sample to occur at the end of infusion. Other nominal time points will be unchanged. Document timing of infusion interruption in eCRF. |
| Interruption in low-rate infusion  | Restart infusion as quickly as practical. Document timing of infusion interruption in eCRF.                                                                                                                                                                                                                                                                                    | Restart infusion as quickly as practical. Document timing of infusion interruption in eCRF. | Restart infusion as quickly as practical. If total interruption $> 30$ minutes in any q4h dosing cycle, subject to be withdrawn and replaced. Document timing of infusion interruption in eCRF.                                                                                                                                                                                    |

## 9. ASSESSMENT OF SAFETY

Any AE reported from the time written informed consent is obtained until completion of the final EOS or ET assessments, regardless of the association with study drug, shall be recorded in the source documents and on the appropriate eCRF page. The AE time of onset (24-hour clock), duration, causality, action taken, and follow-up procedures will be recorded.

### 9.1. Definitions

#### 9.1.1. Adverse Event

An AE is any untoward medical occurrence associated with the use of a drug in humans, whether or not considered drug related (Code of Federal Regulations [CFR] Title 21, Part 312.32[a]). The occurrence does not necessarily have to have a causal relationship with this treatment. An AE can therefore be any unfavorable and unintended sign (for example, an abnormal laboratory

finding), symptom, or disease (new or exacerbated) temporally associated with the use of a drug, whether or not considered related to the study drug.

TEAEs are events that are not present at baseline, or if present at baseline, have worsened in severity after the administration of the first dose of any drug in the study regardless of causality.

### **9.1.2. Life-threatening Adverse Event**

An AE is considered “life-threatening” if, in the view of either the Investigator or Sponsor, its occurrence places the subject at immediate risk of death. It does not include an AE that, had it occurred in a more severe form, might have caused death.

### **9.1.3. Serious Adverse Event**

An AE is considered “serious” (that is, an SAE) if, in the view of either the Investigator or Sponsor, it results in any of the following outcomes:

- Death.
- A life-threatening AE (at risk of death at the time of the event).
- Inpatient hospitalization or prolongation of existing hospitalization.
- A persistent or significant disability/incapacity or substantial disruption of the ability to conduct normal life functions.
- A congenital anomaly/birth defect.

Important medical events that may not result in death, be life-threatening, or require hospitalization may be considered serious when, based upon appropriate medical judgment, they may jeopardize the subject and may require medical or surgical intervention to prevent one of the outcomes listed in the SAE definition.

## **9.2. Recording**

Any AE/SAE reported from the time written informed consent is obtained, and after Screening until the completion of the final EOS or ET assessments, regardless of the association with the study drug, shall be recorded in the source documents and on the appropriate eCRF page.

The Investigator should review all documentation (e.g., hospital progress notes, laboratory, or diagnostic reports) relative to the event being reported. The Investigator will then record all relevant information regarding an AE/SAE on the appropriate eCRF page. It is not acceptable for the Investigator to send photocopies of the subject’s medical records in lieu of completion of the appropriate AE/SAE on all appropriate study documents. However, there may be instances when the Sponsor (or its designee) requests copies of medical records for certain cases. In this instance, all subject identifiers will be blinded on the copies of the medical records prior to submission to the Sponsor (or its designee).

For each AE, the Investigator will evaluate and report the onset (date and time), resolution (date and time), intensity, causality, action taken, serious outcome (if applicable), and whether or not it caused the patient to discontinue the study. The Investigator will attempt to establish a diagnosis of the event based on signs, symptoms, and/or other clinical information. In such cases, the diagnosis should be documented as the AE/SAE and not the individual signs and symptoms. In order to classify AEs and diseases, preferred terms will be assigned by the Sponsor or its designee to the original terms entered on the eCRF, using Medical Dictionary for Regulatory Activities (MedDRA) terms.

### 9.3. Severity

The Investigator will assess the intensity of each AE/SAE based on his/her clinical judgment. The intensity of each event should be assigned to one of the following categories:

- Mild:** An event that is easily tolerated by the subject, causing minimal discomfort and not interfering with everyday activities.
- Moderate:** An event that is sufficiently discomforting to interfere with normal everyday activities.
- Severe:** An event that prevents normal everyday activities. Subject may experience intolerable discomfort or pain.

An AE that is assessed as severe should not be confused with an SAE. Severity is a category utilized for rating the intensity of an event; both AEs and SAEs can be assessed as severe. An event is described as ‘serious’ when it meets one of the pre-defined outcomes as described in Section 9.3.

### 9.4. Clinical Laboratory Adverse Events

The Investigator will exercise medical judgment in deciding whether abnormal laboratory values, ECGs, or other assessment are CS.

Abnormal laboratory findings (e.g., clinical chemistry, hematology, coagulation, urinalysis) or other abnormal assessments (e.g., ECGs, vital signs) that are judged by the Investigator as CS will be recorded as AEs or SAEs if they meet the definition of an AE or SAE (as defined in Section 9.1).

### 9.5. Timing

The reporting period for all AEs begins with the subject signing the ICF and ends with the EOS or ET assessments.

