#### **1.2.2.2. Intravenous Nimodipine Infusion**

The therapeutic efficacy of nimodipine has been evaluated in over 500 patients through a wealth of European clinical studies dating back to 1984, utilizing continuous IV infusion of doses equating to 2 mg/h and 3 mg/h. Overall, IV nimodipine has been given to more than 8,200 patients worldwide. The most frequent AE reported in SAH patients was a decrease in BP. Uncommon (incidence between 1 in 100 and 1 in 1,000) adverse drug reactions (ADRs) include rash, headache, tachycardia, hypotension, vasodilation, nausea, thrombocytopenia, and allergic reaction, and rare (incidence between 1 in 1,000 and 1 in 10,000) ADRs include bradycardia, ileus, transient increase in liver enzymes, injection and infusion site reactions, and infusion site phlebitis (NIMOTOP (0.02% Solution for Infusion) [Summary of Product Characteristics], July 2016).

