**Figure 4-1. Study Schematic**

[figure not shown]

EOS = End of Study; PK = pharmacokinetic

Subjects will be admitted to the clinical research unit (CRU) and randomized to a treatment sequence on Day -1. For treatment sequence AB, Treatment 1 will be Treatment A and Treatment 2 will be Treatment B; for treatment sequence BA, Treatment 1 will be Treatment B and Treatment 2 will be Treatment A. Dosing schematics for Treatment A (GTX-104 IV administration) and Treatment B (oral nimodipine) are provided in [Figure 4-2](#) and [Figure 4-3](#), respectively. In each dosing period, study drug administration will begin at approximately 8 AM in fasted status. The 72-hour dosing period will end on Day 4 for the first treatment and Day 11 for the second treatment, at 4 AM (oral nimodipine) or 8 AM (GTX-104). The washout period will be at least 96 hours. EOS assessments will begin after the final PK assessments of the second treatment period. A detailed study assessment schedule is provided in [Table 4-1](#).

Note that the overall study days provided in the figure assume the minimum washout period of 96 hours. The washout period may be extended as long as study drug initiation occurs at the same time of day (approximately 8 AM). If the washout period is extended, the overall numerical study day for Treatment 2 and the EOS assessments will be different than those presented above.

Nimodipine will be administered based on each subject's randomized treatment schedule: AB or BA, where Treatment A is GTX-104 administered as a 72-hour continuous infusion at 0.15 mg/h in addition to 4 mg administered over 30 minutes q4h (total drug infused over 30 minutes every 4 hours = 4.075 mg, and total drug infused every 4 hours = 4.6 mg), and Treatment B is 60 mg oral nimodipine administered q4h for 72 hours (18 total doses).

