## **4.2. Scientific Rationale for Study Design**

This is a standard crossover study designed to evaluate the relative BA at steady state of two formulations of nimodipine: GTX-104 (nimodipine for IV infusion; test formulation) and nimodipine oral capsules, RS (reference formulation). A crossover design was selected to reduce the impact of inter-subject variability in PK analysis. The design is in accordance with the most current guidance from the U.S. Food and Drug Administration (FDA), [FDA Bioavailability Studies Submitted in NDAs or INDs — General Considerations: FDA Guidance for Industry, 2019](#).

The washout period of at least 96 hours was selected based on the half-life of nimodipine to limit the possibility of study drug carryover effects.

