For both Treatment A and Treatment B, baseline (prior to first dose) BP determination will be taken via oscillometric sphygmomanometer. On Days 3 and 10, 1 hour post dose BP determinations will be performed after the 8:00 AM, 12:00 PM, 4:00 PM and 8:00 PM doses, as described in [Section 8.10](#).

Any new AEs that occur after treatment administration will be attributed to the formulation administered in that dosing period. Any new AEs that occur during washout will be attributed to the treatment administered during the first dosing period.

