#### **4.3.4. End of Study/Early Termination (Day 11)**

EOS assessments should be completed after the final PK sample collection and prior to subject discharge from the CRU, as described in the Time and Events Schedule ([Table 4-1](#)). In the event of Early Termination (ET), EOS assessments should be attempted, if the subject consents. ET assessments should include collection of a blood sample for PK analysis; the PK time point closest to the ET time and the relative dosing day shall be recorded in the appropriate eCRF.

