### **6.3. Timing of Dose**

On Days 1 to 4 of each treatment period, study drug will be administered at the same time each day (starting at approximately 8 AM on Day 1). The time of dosing will be standardized to avoid effects of diurnal variation between dosing periods.

For GTX-104, the 30-minute 4 mg infusion should be started at the same time in the morning (e.g., 8 AM) as the 0.15 mg/h continuous infusion. The 4 mg infusion should be administered q4h starting on Day 1 (e.g., 8 AM, 12 PM, 4 PM, 8 PM, 12 AM, 4 AM) for a total of 18 infusions of the 4 mg dose. The continuous infusion should be stopped on Day 4 after 72 hours (e.g., approximately 8 AM).

Oral nimodipine will be administered at a dose level of 60 mg (two 30 mg capsules) q4h starting at approximately 8 AM on Day 1 of the dosing period, for a total of 18 doses (e.g., 8 AM, 12 PM, 4 PM, 8 PM, 12 AM, 4 AM).

The time of the washout period will be different for each treatment sequence (AB or BA). For the AB treatment sequence, the washout will be at least 96 hours. However, for the BA treatment sequence, as the final dose of oral nimodipine is given at 4 AM on Day 4, the washout duration will be at least 100 hours. In all cases, washout should meet or exceed a minimum of 96 hours.

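### New non-serious AEs that start after End of Study are not collected, so post-dose AE observation is about 0 to 4 hours in Period 2 against at least 96 to 100 hours in Period 1

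*Protocol*

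**What the plan says.** - Section 9.5 sets the AE window: "The reporting period for all AEs begins with the subject signing the ICF and ends with the EOS or ET assessments". The opening of Section 9 and Section 9.2 give the same end point.
- Section 4.3.4 places that end point: "EOS assessments should be completed after the final PK sample collection and prior to subject discharge from the CRU". Table 4-1 lists no visit or call after it.
- The last PK sample is at 72 h for both treatments (Section 8.11.1). The GTX-104 infusion also ends at 72 h, and the last oral dose is given 4 h earlier (Section 6.3).
- In Period 1, AE assessment runs on through washout (Table 4-1), and Section 4.3.3.1 adds: "Any new AEs that occur during washout will be attributed to the treatment administered during the first dosing period".
- Section 9.6 follows AEs already documented as ongoing for up to 4 weeks after the last visit.
- Section 9.8 first requires every SAE to be reported, related or not, whenever it occurs once dosing has begun. Later, for the time after EOS, it speaks only of causally related SAEs that the investigator happens to learn of.
- Safety is the secondary objective (Section 2.2). TEAE incidence by treatment is a stated endpoint (Section 3.3) and is to be summarised for each treatment (Section 10.6).

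**The concern.** A crossover summary by treatment assumes that an exposure is watched in much the same way whichever period it falls in. Here a Period 1 exposure is watched through dosing and the whole washout, while a Period 2 exposure is watched through dosing and little more. The two are then pooled under one treatment heading.

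New non-serious AEs that begin after EOS have no collection route. The protocol lists among the rare reactions to IV nimodipine "bradycardia, ileus, transient increase in liver enzymes, injection and infusion site reactions, and infusion site phlebitis". A site reaction first noticed once the line is out would be recorded if GTX-104 came first and not recorded if it came second. A SAP can define the window used for analysis, but it cannot recover events that were never asked about.

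The SAE wording is a second, smaller matter. A site reading Section 9.5, the start of Section 9.8 and the end of Section 9.8 would find three different rules for an unrelated SAE after EOS.

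**Working it through.** **Inputs.** Dosing starts at 8 AM on Day 1. Period 2 starts at 8 AM on Day 8 at the minimum washout. The infusion ends at 72 h; there are 18 oral doses, one every 4 h (Section 6.3). The final PK sample is at 72 h (Section 8.11.1). Allocation is 1:1 (Section 6.4). At least 60 subjects are enrolled to give 50 completers (Section 10.2).

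**1. The protocol's own washout figures.** Day 1 to Day 8 is 7 × 24 = 168 h. The 18th oral dose falls at 17 × 4 = 68 h. The washout is 168 − 72 = 96 h after GTX-104 and 168 − 68 = 100 h after oral. Both match Section 6.3.

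**2. Post-dose AE observation and total window per exposure** (Period 2 excludes the time taken by EOS procedures):

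| Treatment | Period | After last dose or end of infusion | First dose to end of window |
|---|---|---|---|
| GTX-104 | 1 (sequence AB) | at least 96 h | 72 + 96 = 168 h |
| GTX-104 | 2 (sequence BA) | 72 − 72 = 0 h | 72 h |
| Oral | 1 (sequence BA) | at least 100 h | 68 + 100 = 168 h |
| Oral | 2 (sequence AB) | 72 − 68 = 4 h | 68 + 4 = 72 h |

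**3. Share of exposures affected.** With 1:1 allocation and every subject dosed in both periods, 30 of 60 exposures to each treatment (25 of 50 completers) fall in Period 2, so half are truncated.

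**4. Post-dose person-hours, 60 subjects, minimum washout.**
- GTX-104: 30 × 96 + 30 × 0 = 2,880, against 60 × 96 = 5,760 with equal follow-up (50%).
- Oral: 30 × 100 + 30 × 4 = 3,120, against 60 × 100 = 6,000 (52%).

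**5. Balance between treatments.** The mean window per exposure is (168 + 72) / 2 = 120 h for each treatment.

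**6. What is still captured after EOS.** Set side by side:
- Section 9.6 covers events already recorded.
- The start of Section 9.8 covers all SAEs but sets up no active collection.
- The end of Section 9.8 covers related SAEs that become known.
- None of these covers a new non-serious AE, and the two statements in Section 9.8 disagree on an unrelated SAE.

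**The case against.** The case for leaving the plan alone has real weight.

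- **EOS is a proper safety check.** It includes an abbreviated examination that covers the skin, vital signs, an ECG and laboratory tests (Section 8.4, Table 4-1). A site reaction visible by then is recorded and followed. This stands; only onset after EOS is at issue.
- **The named local reactions are rare.** Section 1.2.2.2 puts them between 1 in 1,000 and 1 in 10,000. If those rates carried over, 60 exposures would give 60 × 0.001 = 0.06 down to 60 × 0.0001 = 0.006 events per reaction type. If every onset followed the infusion, half would be lost: 0.03 down to 0.003. The rates belong to another formulation, so they are only a guide, but nothing in the protocol supports a large loss.
- **Exposure falls quickly.** Section 1.3.2 gives a distribution half-life of 1 to 2 hours and expects concentrations to drop rapidly once the infusion stops. A reader might take "The washout period of at least 96 hours was selected based on the half-life of nimodipine" to mean that the drug still acts for 96 h. It does not say so: Section 4.2 gives the washout as protection against carryover.
- **The analysis window may be left to the SAP.** Section 10.1 allows this. It does not answer the collection gap.

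The unequal observation and the missing route for new non-serious AEs survive these points.

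**Conclusion.** The point holds and is minor. For half the exposures to each treatment, new non-serious AEs are collected for about 0 h (GTX-104) or 4 h (oral) after the last dose, plus EOS procedures, against at least 96 h or 100 h for the other half. TEAE incidence by treatment mixes windows of about 168 h and 72 h and can under-count late-onset events. Post-EOS SAE reporting is worded inconsistently. The figures assume the minimum washout, equal sequences and no dropout. The number of events lost cannot be computed, because the protocol gives no rate of delayed onset.

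Stronger readings that a reader might infer, and that the protocol does not support:

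- **That the comparison is materially biased in favour of GTX-104.** The 1:1 sequences truncate both treatments almost equally; the only built-in difference is the 4 h oral offset.
- **That collection always closes as the infusion stops.** This fits sequence BA only. In sequence AB, Period 2 is oral.
- **That all delayed events are lost.** Ongoing AEs and at least related SAEs that become known remain covered.
- **That liver-enzyme rises are missed in Period 2 but seen in Period 1.** Table 4-1 schedules no laboratory tests during washout; the only scheduled post-dose chemistry is at EOS, and a telephone call would not detect a silent rise.
- **That the 30-day pregnancy window bears on this.** Section 8.15.2 is a separate reporting duty.

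**What to change.** 1. In Sections 9.2 and 9.5 and Table 4-1, extend AE and SAE collection to at least 96 h after the last Period 2 dose, through one telephone contact that asks about new AEs, their onset times and the infusion site. Align the opening of Section 9.
2. Reconcile Section 9.5 with the two statements in Section 9.8, so that a single rule says which SAEs are reported after EOS and until when.
3. Summarise TEAEs by treatment over the same window in both periods, from first dose to 96 h after the last dose, and list later washout events separately. If no contact is added, use first dose to 72 h in both periods for the summary by treatment and list washout events separately. This rule can sit in the SAP.

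The cost is one call per subject, a few sentences of amendment and some programming. Dosing, PK sampling and the primary analysis do not change.
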